##### La Vida Buena intervention

The LVB team includes two CHWs, a CHW coordinator, a health promotion manager at the FQHC, two evaluators based out of a nearby university, and two adolescent peer educators. The La Vida Buena intervention, delivered by teams of adult Community Health Workers (CHWs) and adolescent peer health educators (Teen Health Facilitators), takes place once a week for 8 weeks. Each weekly hour-long session includes 20 min of interactive learning topics, 20 min of physical activity and 10 min of healthy food preparation and discussion. All activities are designed to encourage active learning from both the parents and the children. The interactive learning topics focus on nutrition, physical activity and healthy family habits. Teen health facilitators lead the physical activity portion of the class. The objectives of each class session and selected activities are listed in Table 1.

**Table 1 Tab1:** La Vida Buena curriculum session objectives

Session Name	Objectives	Example activities, incentives and food demonstrations
Session 1: Orientation	• Identify the program goals: Increase fruit and vegetable consumption; Increase non-school physical activity; Reduce sugary drink intake and other refined carbohydrates • Identify two health issues related to being overweight • Recognize La Vida Buena as an informative and fun program	• Physical activity through play • Incentive: jump ropes • Food demo: fruit salad
Session 2: Gotta Love those Fruits and Veggies	• Name GO FOODS - to eat almost anytime (Fruits and veggies) • Identify SLOW FOODS - to eat less often (Grains, dairy, protein) • Name WHOA FOODS - to eat once in a while (High caloric, high fat foods) • Express one strategy to eat in a more healthy manner	• Go/Slow/Whoa traffic light game • Incentive: fruit/veggie stuffed animals and measuring cups • Food demo: DIY salad bar
Session 3: Guess what’s in the bowl	• Understand what a serving size is • Understand MyPlate	• Guess how much is in the cereal bowl • Incentive: MyPlate plate, smoothie cup • Food demo: cauliflower rice
Session 4: Breakfast for your Brain	• Identify breakfast as the most important meal of the day • Identify a healthy cereal by label reading based on fiber and sugar contents • Write one healthy breakfast menu as a family	• Label detective with magnifying glasses • Incentive: balls and Tupperware set • Food demo: apple “cookies”
Session 5: Physical Activity with 0S3 biking group	• Identify the benefits of bicycling • Identify opportunities to use their bikes • Name two safety rules when bicycling	• Biking activity circuit • Incentives: bike helmets • Food demo: Fruit kebab stick
Session 6: Water Your Way	• Read beverage nutrition facts labels • Name one benefit of drinking water and skim milk • Learn how much sugar is in popular drinks	• How much sugar do you pour into your bodies? • Incentives: water bottles • Food demo: infused water
Session 7: Shopping Like Pros	• Learn to navigate the supermarket • Identify strategies to be prepared for grocery shopping • Read nutrition facts label	• Choose a meal from the La Vida Buena ‘supermarket’ • Incentives: shopping list and chef hat • Food demo: avocado toast
Session 8: My Mexican Food is Healthy	• Identify one strategy to cook healthier • Modify one recipe by adding, reducing, substituting, or eliminating to create a healthier recipe • Express one benefit of eating together	• Make abuelita’s recipe healthier • Incentives: crock pot • Food demo: yogurt parfait

Culturally responsive educational tools and incentives are intended to maximize participation, reinforce learning objectives and increase participant retention. Teaching tools include MyPlate plates, plastic foods, posters, and magnifying glasses to ‘investigate’ labels, among other items. Incentives include items such as jump ropes, cooking utensils, cookbooks and water bottles.

#### Comparison group

The comparison group is drawn from a satellite clinic in a neighboring community. The characteristics of the pediatric population are similar in both clinics. CHWs deliver a 50-min educational session either one-on-one or in a group setting. The educational session includes 40 min of interactive learning activities focused on nutrition and 10 min of physical activity information, and focuses on some of the basic strategies and key messages covered in the 8-week La Vida Buena intervention. The CHW facilitator discusses nutrition and physical activity strategies with the parent and child in a single educational session, but the session is more didactic and does not include a physical activity session. The session objectives for the comparison group are listed in Table 2.

**Table 2 Tab2:** Learning Objectives for Comparison Group Single Educational Session

Session	Objectives
Comparison Group Education Session	By the end of the session participants will be able to: • Identify Go foods - to eat almost anytime (Fruits and Veggies) • Identify Slow foods - to eat sometimes (Grains, Dairy, Protein) • Identify Whoa foods - to eat once in a while (High caloric, High fat foods) • Identify the recommended daily fruit and vegetables portions

The FQHC will offer the full LVB intervention to participants in the comparison group following the completion of data collection.

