## Methods: recruitment

### Sample size

To detect a minimal important difference of 0.2 BMI z-standardized units between baseline and 6-month follow-up, an estimated sample size of *n* = 200 participants is required. This calculation assumes 100 participants for the intervention site and 100 participants for the comparison site, with a 25% attrition rate, in order to achieve 80% power. The power calculation was completed using ANCOVA simulations with a type 1 error rate of 5% and a standard deviation in group differences of 0.4 BMI z standardized units.

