### Recruitment and retention

Participants are recruited through the FQHC clinics. Medical providers refer patients who are eligible for the program based on the inclusion criteria. Medical assistants, care coordinators, and CHWs work collaboratively to invite participants at doctor’s appointments, or by printed invitations, telephone calls and/or the patient portal. The LVB study team also created flyers and brochures that can be provided to potential participants. The CHWs who coordinate and facilitate the program call to confirm their participation and begin to build relationships with the participants before the first class.

Based on an intent to treat analysis, once enrolled in the program, each family is considered a participant for post and follow up measure, regardless of the extent to which they engage in La Vida Buena curriculum. Study staff remind participants of the weekly activities and keep in touch with participants throughout the program through phone calls and text messages. The FQHC has identified strategies, such as the incentives, to keep participants engaged in the La Vida Buena program activities. We also offer childcare and transportation to the families to reduce potential barriers to attending the class. Parent participants are provided with a $25 gift certificate to a local grocery store upon completion of both the post and follow-up measures.

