#### Primary analysis

The primary endpoint will be change BMI z-score from baseline to 6 months follow up among subjects participating in the program La Vida Buena compared to those receiving an educational class. BMI z-scores will be modeled using an analysis of covariance (ANCOVA) model. Let BMI_*ijk*_ represent the BMI z-score for the *j*^*th*^ subject in the *i*^*th*^ treatment group at the *k*^*th*^ time point for *k* ∈ {0, 1, 2}. The *k* levels for time point correspond to baseline (k = 0), 3 months follow up (k = 1), and 6 months follow up (k = 2). The ANCOVA model is specified as,$$ {\mathrm{BMI}}_{ij2}={\mathrm{BMI}}_{ij0}+{T}_i+{\epsilon}_{ij2} $$where *T*_*i*_ is the intervention effect for and *ϵ*_*ij*2_ is the error term. The effect *T*_*i*_ will be tested at the *α* = 0.05 significance level and the effect size along with a 95% confidence interval will be reported.

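### The intervention is taught in classes but the primary ANCOVA has no class term, so any positive within-class correlation makes the 95% CI too narrow and lifts the type I error above 5%

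*Protocol article*

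**What the plan says.** **Delivery, intervention arm.** The section on the La Vida Buena intervention describes weekly hour-long sessions over 8 weeks, "delivered by teams of adult Community Health Workers (CHWs) and adolescent peer health educators (Teen Health Facilitators"). Table 1 lists shared games, physical activity and food demonstrations. The recruitment and qualitative sections also refer to the programme as a class. Neither the class size nor the number of classes is given.

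**Delivery, comparison arm.** The Comparison group section says that "CHWs deliver a 50-min educational session either one-on-one or in a group setting". The split between the two formats is not given.

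**Analysis.** The Primary analysis section writes the model out: 6-month BMI z-score on baseline BMI z-score, a treatment effect and one error per subject. The treatment effect is tested at the 0.05 "significance level and the effect size along with a 95% confidence interval will be reported". The Secondary analysis section applies the same model to the four secondary outcomes. Neither model has a term for class or session.

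**Sample size.** The inputs are a difference of 0.2, an SD of 0.4, a 5% type I error, 25% attrition and 100 children per site, "in order to achieve 80% power". No ICC, class size or design effect is mentioned.

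**Unit.** Under Recruitment and retention, "each family is considered a participant for post and follow up measure".

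**The concern.** Children in one 8-week class share classmates, a calendar period, the sessions as delivered and whatever group dynamic develops. Their 6-month outcomes may therefore be more alike than those of children from different classes. A model with one error per child counts them as fully separate pieces of information. If the correlation is positive, the standard error of the treatment effect is too small, the 95% interval covers less than 95% of the time, and the test rejects a true null more than 5% of the time. The comparison arm may be clustered less or not at all, so the problem can differ by arm.

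This bears on the trial's main result, and the error runs towards a false positive. A larger sample does not cure it: with the class size held fixed, the inflation of the type I error is the same at any number of children.

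**Working it through.** **Inputs from the Sample size section:** difference 0.2, SD 0.4, alpha 5%, power 80%, 100 per arm, 25% attrition, hence 100 × 0.75 = 75 completers per arm. The test is taken as two-sided, because "the effect size along with a 95% confidence interval will be reported".

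**Assumptions, not in the documents:** class size m = 10 among completers and ICC from 0.01 to 0.10; a wider grid with m from 5 to 15 is also given.

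**1. The plan's own figure.**
- n per arm = 2 × [0.4 × (1.960 + 0.842) / 0.2]² = 62.8, so 63.
- With attrition, 63 / 0.75 = 84 per arm, 168 in total, against 200 stated.
- With 75 per arm the independent-errors SE is 0.4 × √(2/75) = 0.0653. Power = Φ(0.2/0.0653 − 1.960) = Φ(1.102) = 86.5%, against 80% stated.

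The stated 200 is therefore not reproduced, but it lies on the safe side.

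**2. Spare capacity.** 75 / 62.8 = 1.19. A correctly analysed trial keeps 80% power up to that overall design effect. At m = 10 this corresponds to an ICC of 0.194 / 9 ≈ 0.02 if both arms are grouped, or 2 × 0.194 / 9 ≈ 0.04 if only the intervention arm is.

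**3. Type I error of the planned test.** The design effect within a grouped arm is D = 1 + (m − 1) × ICC. Overall it is D if both arms are grouped and (D + 1)/2 if only one is. The true SE is √(design effect) times the one that the model reports, so the actual alpha is 2 × [1 − Φ(1.960 / √design effect)].

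For m = 10:

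| ICC | One arm: design effect | One arm: alpha | Both arms: design effect | Both arms: alpha |
|---|---|---|---|---|
| 0.01 | 1.045 | 5.5% | 1.09 | 6.0% |
| 0.02 | 1.09 | 6.0% | 1.18 | 7.1% |
| 0.05 | 1.225 | 7.7% | 1.45 | 10.4% |
| 0.10 | 1.45 | 10.4% | 1.90 | 15.5% |

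Simulating the ANCOVA with 75 per arm and m = 10 gave 5.0% at ICC 0. At the four ICCs above it gave 5.5%, 5.7%, 7.4% and 10.2% with one arm grouped, and 5.7%, 7.0%, 9.7% and 15.6% with both.

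**4. Wider grid.** Over m from 5 to 15 and ICC from 0.01 to 0.10, alpha runs from 5.2% to 20.6%. The correct interval is 1.01 to 1.55 times as wide as the planned one.

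**5. Power at m = 10, ICC 0.05.** Two tests have to be kept apart.
- Planned test, clustering ignored: Φ[(0.2 − 1.960 × 0.0653) / (0.0653 × √design effect)] gives 84.0% (one arm) or 82.0% (both arms).
- Test with the cluster-corrected SE: Φ[0.2 / (0.0653 × √design effect) − 1.960] gives 79.0% or 72.0%.

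The planned test keeps its power partly because it rejects too often.

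**6. Number of classes.** 75 / 10 = 7.5, so about 8 classes in the intervention arm. A class-level test has few degrees of freedom, and the normal approximation in step 5 flatters the corrected test slightly.

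**The case against.** **The size is unknown.** This stands. Without an ICC or a class size, the excess over 5% could be negligible: the grid starts at 5.2%. The team has two CHWs, who probably recur across classes, and fidelity is monitored against a threshold; both would limit differences between classes. If 10 children enrol per class and 25% leave, m is 7.5, and the one-arm figure at ICC 0.05 falls from 7.7% to 6.9%.

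**The both-arms figures are an upper case.** This stands too. They assume that every comparison child is taught in a group and that one 50-minute session leaves the same ICC at 6 months as eight weekly classes. If the comparison sessions are mostly one-on-one, the one-arm column is the relevant one.

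**The error structure could be left to an analysis plan.** This stands only in part. The equation is abbreviated, with no intercept and no baseline coefficient. But the article does not leave the model open: it writes out the terms and attaches the test and the interval to them.

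**Stronger readings that the article does not support.**
- A reader might infer that siblings enter as independent observations, because the family is called the participant while the model indexes subjects. No section says that siblings are enrolled, and the eligibility criteria speak of a single child. With one child per family, enrolment by family adds no correlation.
- A reader might infer that the trial is underpowered. The stated inputs need only 168, and the planned test stays above 80% at ICC 0.05 with m = 10.
- A reader might infer that the power simulations assumed independence. The article is silent on this, and the unexplained margin between 168 and 200 could have several sources.

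**Conclusion.** The point holds conditionally. The article fixes a model without a class term for an intervention taught in classes. If the within-class correlation is positive, the interval is too narrow and the type I error exceeds 5%. With 10 per class, 75 completers per arm and ICC 0.01 to 0.10, the type I error is about 5.5% to 10.4% with only the intervention arm clustered and 6.0% to 15.5% with both. These ranges rest on an assumed ICC and class size, so an inflated error rate is a risk that the plan leaves open and not an established fact. Power is secondary, since 200 tolerates a design effect of about 1.19. A concern about siblings arises only if siblings are in fact enrolled.

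**What to change.** - Record a class or session identifier for every child in both arms, and whether a comparison child was taught one-on-one or in a group.
- Replace the ANCOVA, for the primary and the secondary outcomes, with a partially nested mixed model: the same baseline and treatment terms, a random class effect for group-taught children, one-on-one children as their own clusters, and small-sample degrees of freedom (for example Kenward-Roger).
- State the assumed ICC and class size beside the power figure.
- Say whether siblings can enrol. Only if they can, add a family effect or use one index child per family.

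**Cost.** One or two data fields, some analysis wording and a somewhat wider interval: about 1.11 times as wide at m = 10 and ICC 0.05 with one arm grouped (√1.225), before the small-sample correction. Class membership should be captured before analysis, since it may be hard to reconstruct later.

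**What it does not solve.** Each arm comes from one clinic (Justification for study comparators and design), so this model still cannot separate the treatment effect from a clinic effect. That limitation is separate and should be stated as such.

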#### Intervention Fidelity

An academic evaluator and the LVB coordinator established definitions and expectations for intervention fidelity using a participatory process. They observed and rated the delivery of selected sessions using a fidelity checklist based on session objectives, facilitator skills, and participant responses. The pair iteratively compared and resolved rating differences until they had established 80% inter-rater agreement in every session. For the remainder of the intervention and comparison sessions a single observer attends and evaluates at least 20% of the sessions, using a 5-point Likert scale to assess intervention delivery and response. Fidelity is considered an average of 4.0 or above for each scale.

## Methods: recruitment

### Sample size

To detect a minimal important difference of 0.2 BMI z-standardized units between baseline and 6-month follow-up, an estimated sample size of *n* = 200 participants is required. This calculation assumes 100 participants for the intervention site and 100 participants for the comparison site, with a 25% attrition rate, in order to achieve 80% power. The power calculation was completed using ANCOVA simulations with a type 1 error rate of 5% and a standard deviation in group differences of 0.4 BMI z standardized units.

### Eligibility criteria

Study inclusion criteria include: [1] age of child (5–8 years old), [2] BMI of child above 85th percentile for age and sex, [3] participation of an adult parent or caregiver who is 18 or older, and [4] signed consent from the parent or guardian. All intervention activities are completed in Spanish, so both the parent and child must speak and understand Spanish.

### Recruitment and retention

Participants are recruited through the FQHC clinics. Medical providers refer patients who are eligible for the program based on the inclusion criteria. Medical assistants, care coordinators, and CHWs work collaboratively to invite participants at doctor’s appointments, or by printed invitations, telephone calls and/or the patient portal. The LVB study team also created flyers and brochures that can be provided to potential participants. The CHWs who coordinate and facilitate the program call to confirm their participation and begin to build relationships with the participants before the first class.

Based on an intent to treat analysis, once enrolled in the program, each family is considered a participant for post and follow up measure, regardless of the extent to which they engage in La Vida Buena curriculum. Study staff remind participants of the weekly activities and keep in touch with participants throughout the program through phone calls and text messages. The FQHC has identified strategies, such as the incentives, to keep participants engaged in the La Vida Buena program activities. We also offer childcare and transportation to the families to reduce potential barriers to attending the class. Parent participants are provided with a $25 gift certificate to a local grocery store upon completion of both the post and follow-up measures.

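### The primary ANCOVA has 6-month BMI z as its only response, so the 3-month value that is collected cannot protect the estimate if dropout works differently in the two arms

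*Protocol article*

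**What the plan says.** Four parts of the protocol article bear on this point.

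- **Recruitment and retention:** "Based on an intent to treat analysis, once enrolled in the program, each family is considered a participant for post and follow up measure". The sentence goes on to say that this holds however much of the curriculum the family takes up.
- **Sample size:** "100 participants for the intervention site and 100 participants for the comparison site", "with a 25% attrition rate, in order to achieve 80% power".
- **Outcome data collection:** height and weight are measured at baseline, 3 months (one month after the classes end) and 6 months.
- **Primary analysis:** the time index is defined in full ("levels for time point correspond to baseline (k = 0), 3 months follow up (k = 1" and 6 months as k = 2). The model that follows has the 6-month BMI z on the left and only baseline BMI z, the treatment effect and an error term on the right.

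No k = 1 term appears in the primary model. The Secondary analysis section gives the same form, with a 6-month response adjusted for baseline, to the other outcomes. The article names no missing-data method, and it does not say that children without a 6-month value are excluded.

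**The concern.** A model whose only response is the 6-month value cannot use a child who was measured at baseline and 3 months and then lost. The estimate then comes from those who stay. That is harmless if dropout is random, or if it depends on early response in the same way in both arms. It is not harmless if the dependence differs by arm.

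Different dependence is plausible here. One arm is asked to attend eight weekly classes; the other attends one session and is offered the full programme after data collection. The arms are different communities and are not randomised. The Background itself cites a review that found lower retention in trials of this kind. If families whose child is not responding leave the eight-week arm, the remaining children make the programme look better than it is.

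The 3-month BMI z is the measurement closest in time to the missing one, and the plan already pays for it.

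**Working it through.** **1. Children analysed as written.** 200 × (1 − 0.25) = 150, or 75 per arm.

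**2. The plan's sample size, and power with 75 per arm.** Inputs from the Sample size section: difference 0.2 ("To detect a minimal important difference of 0.2 BMI z-standardized units between baseline and 6-month follow-up"), SD 0.4 ("a standard deviation in group differences of 0.4 BMI z standardized units", taken as the per-child SD because the wording leaves this open), 5% type 1 error, 80% power. Two-sided testing is assumed from the 95% confidence interval.

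- n per arm = 2 × (1.960 + 0.842)² × (0.4 / 0.2)² = 62.8, so 63. Then 63 / 0.75 = 84 per arm, 168 in total. The stated 200 is not reproduced. The gap is on the conservative side, may reflect simulation settings not given, and does not bear on this point.
- Power at 75 per arm: 0.2 / (0.4 × √(2/75)) = 0.2 / 0.0653 = 3.06; 3.06 − 1.96 = 1.10; Φ(1.10) ≈ 0.86.

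Loss of power is therefore not the problem.

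**3. Size of the bias.** The documents give no arm-specific dropout, so everything here is assumption: 100 per arm, about 25% lost in each arm, residual SD 0.4 at 3 and 6 months, residual 3-to-6-month correlation ρ, 2,000 simulated trials per case. In the one-arm case the log-odds of dropout in the intervention arm rise by 0.8 per SD of unfavourable 3-month change (odds × e^0.8 = 2.2), and comparison dropout is random. The effect is intervention minus comparison, so negative favours the programme. The alternative estimator fits the 3-month value on baseline and arm, fits the 6-month value on the 3-month value, baseline and arm, and combines the two.

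True effect 0, every dropout measured at 3 months, one-arm dependence:

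| ρ | Completers ANCOVA | False-positive rate (nominal 5%) | Using 3-month value |
|---|---|---|---|
| 0.5 | −0.035 | 8% | about 0.00 |
| 0.7 | −0.049 | 13% | about 0.00 |
| 0.85 | −0.061 | 15% | about 0.00 |

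As a consistency check, the bias should equal ρ × 0.4 × m, where m is the mean standardised 3-month residual among retained intervention children. The ρ = 0.7 row gives m = −0.049 / (0.7 × 0.4) = −0.175. Then 0.5 × 0.4 × (−0.175) = −0.035 and 0.85 × 0.4 × (−0.175) = −0.060, in line with the other two rows.

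With a true effect of −0.20, the completers ANCOVA averages −0.235 to −0.258 over the same range of ρ, and the estimator with the 3-month value about −0.20.

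**4. Other dropout patterns** (true effect 0, ρ = 0.6):

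| Pattern | Completers | Using 3-month value |
|---|---|---|
| Same dependence in both arms | 0.002 | 0.001 |
| Slope 0.8 in one arm, 0.4 in the other | −0.021 | – |
| Slope 0.4 in one arm, 0 in the other | −0.024 | – |
| Slope 0.8 in one arm only, all dropouts seen at 3 months | −0.045 | −0.002 |
| As above, half of dropouts also miss 3 months | −0.043 | −0.018 |
| As above, all dropouts also miss 3 months | −0.040 | −0.040 |

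**5. Cost in precision when dropout is random.** Both methods are unbiased. With every dropout seen at 3 months, the standard error goes from 0.065 to 0.063 (ρ = 0.5), 0.064 to 0.061 (0.7) and 0.064 to 0.058 (0.85). With half seen, it is unchanged at ρ = 0.5 and slightly smaller at the higher correlations.

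**The case against.** A reader might infer that the plan breaks its own intent-to-treat commitment. It does not. The sentence concerns measuring families whatever their attendance. Not attending classes is different from having no measurement, and an ANCOVA by arm as enrolled is consistent with it.

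A reader might also infer that the plan discards dropouts as a matter of policy. That is not stated either. Imputing before the ANCOVA would be compatible with the model, and such handling is commonly left to an analysis plan, which is not shown here. Silence on imputation is therefore no finding. What remains is the choice the article does fix: a single-time-point response, beside a defined and collected 3-month value that no stated analysis uses.

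Baseline-adjusted ANCOVA at the primary time point is a standard method, and the bias figures depend on assumed dropout. With equal dependence in both arms there is nothing to correct, and with milder differences the bias is about half as large. The plan also has reminders, childcare, transport and a gift certificate to hold retention up. All of this stands, and it limits the severity.

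The repair is limited too. The 3-month visit comes after the classes end, so families who leave during the eight weeks may have no 3-month value, and for them the repeated-measures model does nothing.

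**Conclusion.** The point holds as a worthwhile improvement to the primary analysis. It is not an internal contradiction or a defect that invalidates the trial. As written, about 50 of 200 children would contribute nothing, and for those lost after 3 months a relevant measurement would go unused.

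The possible bias runs from about 0 (random dropout, or equal dependence in both arms) to about 0.06 BMI z (dependence in one arm only, ρ = 0.85). At the upper end that is 0.061 / 0.2, about 31% of the target difference. These figures rest on 25% loss, a residual SD of 0.4, correlations of 0.5 to 0.85 and the assumed dropout odds; none of the dropout mechanisms is in the documents. Across the patterns examined, using the 3-month value reduced the bias or left it unchanged, and it did not cost precision.

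**What to change.** Make the primary analysis a mixed model for repeated measures: 3- and 6-month BMI z as responses, baseline BMI z by visit, arm by visit, and an unstructured covariance between visits. Name the arm contrast at 6 months as the primary estimate, so the endpoint does not change.

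An acceptable alternative is multiple imputation of the 6-month value from baseline and 3-month BMI z within arm, followed by the stated ANCOVA. This keeps every enrolled child in the analysis set, although for a child lost before 3 months the imputation rests on baseline and arm alone.

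In either case, keep the completers ANCOVA as a sensitivity analysis and report how many dropouts in each arm have a 3-month value, because that decides how much the change can repair.

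The cost is a few sentences of analysis text and no new visits. The downsides are a slightly more complex model, reliance on data being missing at random given the 3-month value, and no recovery of children lost before 3 months. Clinic-recorded height and weight could stand in for missed visits, with consent, since the Data management section already foresees consented checks against those records. That is optional and not part of the core change.
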